## Abstract

**Background:**

Malaria is a major health issue that is distributed across 85 countries globally including Indonesia. Indonesia is in the process of achieving malaria elimination. Currently, a high burden of malaria exists in the rural eastern part of the nation, including East Nusa Tenggara Province where the number of malaria cases increased significantly during COVID-19. To achieve malaria elimination, malaria awareness must be measurable and integrated into malaria policy. Currently, malaria awareness among rural communities in the region is low, and interventional studies aiming at improving malaria awareness in rural areas in Indonesia are poorly documented.

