### Outcome Variables

The study considers 10 potential outcomes variables, with the first 7 serving as the primary outcomes of the intervention, while the remaining 3 represent secondary findings. The first primary outcome of the study is improvement in the malaria awareness index among rural communities. If the malaria awareness index after the intervention is higher than that before the intervention, it indicates that the health education campaign effectively enhanced malaria awareness. This index will be assessed based on 12 questions covering general knowledge of malaria, treatment-seeking behavior, and knowledge of malaria prevention measures, following the methodology of a previous study [39]. Each correct response will be assigned a score of 1, while incorrect answers will receive a score of 0, with a total possible score of 12. Participants’ knowledge level will be categorized based on their accuracy rate: 0% (zero awareness), 1% to 59% (poor awareness), 60% to 79% (good awareness), and at least 80% (excellent awareness). Those classified as having excellent or good awareness will be considered aware of malaria, while participants in the other categories will be classified as unaware of malaria [39,70]. The malaria awareness index will be calculated before and after the intervention in both the intervention and control groups to evaluate the effectiveness of the health education campaign.

The second outcome variable in this study is improvement in AMTSB. This improvement will be demonstrated if the proportion of rural adults exhibiting AMTSB after the intervention is higher than before the intervention. AMTSB is defined as seeking malaria treatment at professional health facilities within 24 hours of experiencing malaria symptoms [41]. The proportion of rural adults engaging in AMTSB will be calculated both before and after the intervention in both the intervention and control groups. This assessment will be based on the 3 key questions from the malaria treatment-seeking behavior section of the questionnaire.

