The seventh outcome variable in this study is variation in access to basic drinking water and its associated factors among rural communities in ENT Province, Indonesia. Household access to basic drinking water is defined based on the WHO Joint Monitoring Program guidelines, which classify water sources into 4 categories: no service, unimproved, limited, and basic [75]. To analyze this variable, a dichotomous classification will be used, where households will be categorized as either having access to an improved drinking water source (Yes=1) or lacking access to an improved drinking water source (No=0). This classification will help determine disparities in access to safe drinking water and identify key factors influencing these differences.

The secondary outcomes of this study are derived from the analysis of patient medical records from 4 selected health centers, along with additional data from the Department of Health, East Sumba District. The eighth outcome variable focuses on the monthly number of malaria cases recorded over the past 10 years, from 2013 to 2023. By integrating data from both health centers and the Meteorological Agency of East Sumba, this study aims to explore the impact of climatic variables on malaria case fluctuations in this region, following the methodology of a previous study [76]. This analysis will provide valuable insights into seasonal and long-term trends in malaria transmission, which could help inform future malaria prevention and control strategies.

The ninth outcome variable in this study examines the demographic variations in malaria prevalence among communities residing in hilly and coastal areas over the past 10 years (2013-2023). Among the 4 selected health centers, Baing and Nggongi Public Health centers are located in coastal areas, whereas Mahu and Kananggar Public Health Centers are situated in hilly regions. Given that vector distribution and species composition may vary between different geographic settings [77], previous studies in Indonesia have reported significant differences in malaria prevalence between coastal and hilly areas [78]. By analyzing malaria case records from these health centers, this study aims to assess regional disparities in malaria burden and determine how demographic and environmental factors contribute to these differences. This information may help tailor malaria prevention and control efforts to the specific needs of different geographic regions.

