For the sixth outcome variable, participants’ sociodemographic characteristics, environmental variables, and behavioral aspects of malaria in each group will be reported using descriptive statistics. The association between a good level of MPMP and its predictors will be investigated using chi-square tests. Unpaired samples *t* tests will be used to investigate the statistical differences. Comparations will be performed within and between groups for both pre- and postintervention periods. Moreover, binary logistic regression analysis will be performed to identify the primary risk factors influencing MPMP [73,74] among rural communities in both study groups.

For the seventh outcome variables, descriptive statistics will be used to summarize participants’ sociodemographic characteristics, environmental variables, and malaria-related behaviors based on their source of drinking water. The associations between access to improved drinking water and its predictors will be assessed using chi-square tests. Furthermore, a binary logistic regression model will be used to determine predictors influencing access to improved drinking water [75].

For the eighth outcome variable, descriptive analyses of climatic factors across different subdistricts will be performed. Data will be aggregated at the subdistrict level, and statistical estimates will be generated for each variable. Specifically, the total number of malaria cases and the average malaria incidence will be computed. Climatic variables, including maximum, minimum, and mean temperature values, will be calculated. Moreover, data from all 22 subdistricts will be analyzed, focusing on malaria cases and climatic parameters, including maximum, minimum, and average temperature values. To depict the seasonal dynamics, seasonal variations in climatic parameters and malaria cases will be plotted, covering the 2 main seasons. A time series for both predictor and outcome variables will be plotted to deliver an overall perspective. A map of malaria cases will be generated. Scatterplots will be developed to illustrate relationships between malaria cases and predictor variables, following the methods of a previous study [76].

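### Outcome 8 is framed as the impact of climate on malaria cases, but the stated analysis is descriptive and graphical only and yields no estimate of that impact

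*Protocol article*

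**What the plan says.** In the protocol article, Outcome Variables defines the outcome: "The eighth outcome variable focuses on the monthly number of malaria cases recorded over the past 10 years, from 2013 to 2023". It then gives the purpose, using health-centre and meteorological data: "this study aims to explore the impact of climatic variables on malaria case fluctuations in this region". The outcome is secondary, since the ten outcomes are introduced "with the first 7 serving as the primary outcomes of the intervention, while the remaining 3 represent secondary findings".

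Statistical Analysis describes the work as follows:

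- The opening statement is that "descriptive analyses of climatic factors across different subdistricts will be performed".
- Case totals and mean incidence are computed after aggregation by subdistrict.
- On the climate side, "Climatic variables, including maximum, minimum, and mean temperature values, will be calculated", and then "data from all 22 subdistricts will be analyzed, focusing on malaria cases and climatic parameters, including maximum, minimum, and average temperature values".
- Seasonal plots, time-series plots and a map are produced.
- The step relating cases to climate is "Scatterplots will be developed to illustrate relationships between malaria cases and predictor variables", with a reference to the methods of an earlier published study.

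No regression, effect measure, test, lag or adjustment is stated for this outcome.

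**The concern.** The aim is worded as impact, while the analysis is worded as description. A scatterplot of cases against temperature shows association only. It produces no rate ratio or interval, and it holds neither calendar season, long-term trend nor population size constant.

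Two kinds of wrong reading are possible. Temperature and malaria may share a seasonal cycle, or larger subdistricts may also be warmer or cooler, and a pattern then appears that owes nothing to climate. Conversely, if climate acts with a delay, a plot of concurrent values can hide a real relation. Outcome Variables says this analysis could inform malaria prevention and control strategies, so a plotted pattern could be reported and used as evidence of climate impact.

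**Working it through.** **1. Aim against method.** The protocol gives no sample size, effect size or other figure for outcome 8, so there is nothing to reproduce. The check is a comparison within the Statistical Analysis section.

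| Outcomes | Method stated beyond summaries and plots |
|---|---|
| 1 to 7 | Binary logistic regression (with chi-square tests) |
| 8 | None |
| 9 and 10 | Chi-square tests |

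Outcome 8 is the one outcome with no inferential method, although its aim is worded as impact. The section does mention generating statistical estimates for each variable, but the sentences that follow specify totals, averages and temperature values, which are summaries.

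**2. What each display can separate.**

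- *Season.* Seasonal plots show that cases and climate vary over the year. They do not show whether climate explains cases beyond the calendar cycle.
- *Trend.* Time-series plots make a long-term rise or fall visible. They do not remove it from the scatterplot.
- *Population.* The scatterplot sentence refers to cases, over 22 subdistricts. Expected cases = rate × population. Two subdistricts with the same rate, one with twice the people, differ twofold in cases at any temperature. Mean incidence is also computed, but the scatterplot is not said to use it.

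**3. Length of the series.** If both 2013 and 2023 are counted in full, there are 11 × 12 = 132 months. Over 22 subdistricts that is 132 × 22 = 2,904 subdistrict-months. This assumes that monthly counts exist for every subdistrict.

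**4. Illustration of why season and lag matter.** All parameters here are assumptions, not protocol values.

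(a) For two noiseless annual cycles offset by L months, the same-month correlation is cos(2πL/12):

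- L = 1: 0.87
- L = 2: 0.50
- L = 3: 0.00

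(b) A simulation used 132 months and 2,000 repetitions. Temperature was a unit-amplitude annual cycle plus noise with SD 0.5. Cases were Poisson with log rate 3 + 0.5 × temperature at lag L.

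| True lag | Correlation at the correct lag | Same-month correlation |
|---|---|---|
| 1 month | 0.87 | 0.50 |
| 2 months | 0.87 | 0.29 |
| 3 months | 0.87 | 0.00 |

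A hand check agrees. The cycle has variance 0.5 and the noise 0.5² = 0.25, so the same-month value is roughly 0.87 × 0.5 × cos(2πL/12) / 0.75. For L = 1 this is 0.87 × 0.577 = 0.50. For L = 2 it is 0.87 × 0.333 = 0.29.

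(c) In the same set-up, but with cases following the calendar cycle and temperature having no effect, the same-month correlation averaged 0.69.

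So an unadjusted plot of concurrent values can mislead in either direction. The size in this district is unknown.

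**The case against.** The best defence is that the aim is only to explore, the outcome is secondary, and the article openly calls the work descriptive. It is a condensed article that refers to a published study for method, and lags, offsets and covariates are details often left to a fuller plan. Climate also appears in none of the four stated objectives, and the records predate the August 2024 intervention. All of this stands and limits the weight of the point. It does not remove the mismatch, because the descriptive, graphical method is a choice that the article states at some length.

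Several stronger readings are tempting but unsupported:

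- *That the scatterplots are unlagged.* The article is silent on lag and defers to the cited study. Lag is unspecified, not stated wrongly.
- *That only temperature will be used.* It is the only variable named, but both lists open with the word *including*. Rainfall is unnamed, not excluded, although the plan contrasts dry and wet seasons.
- *That only raw counts are analysed.* Mean incidence is also computed. The doubt concerns the scale of the scatterplot.
- *That the plots say nothing about seasonal or long-term patterns.* The seasonal and time-series plots show these directly. What is missing is attribution to climate.
- *That the pandemic-era rise measures the confounding.* The Abstract says that "the number of malaria cases increased significantly during COVID-19", and the Introduction gives 12,909 cases in 2019 and 15,830 in 2022 (15,830 / 12,909 − 1 = 22.6%). Those are figures for East Nusa Tenggara Province. For East Sumba District the article gives a 2022 count only, so no change over those years can be derived for this series.

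**Conclusion.** The point holds as a mismatch between aim and analysis for one secondary outcome. As written, outcome 8 will describe malaria and climate side by side. It will not estimate the impact of climate, nor separate it from season, trend or subdistrict population. This would remain true if the scatterplots used rates, lagged values and rainfall, because unadjusted plots still do not control for season or trend.

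The conclusion rests on the text of the two sections and not on any calculation. The correlations show that the problem can be material under assumed cycles, noise and lags, but they do not measure bias in the district's data. The campaign's effect on the behavioural outcomes is untouched.

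**What to change.** Choose one of two routes and make Outcome Variables and Statistical Analysis agree.

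**Route 1: estimate the association.** Keep all the plots as description. Add a negative binomial regression of monthly cases by subdistrict with:

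- log population as offset;
- subdistrict effects;
- terms for calendar season and long-term trend;
- the climatic variables available from the Meteorological Agency (temperature, and rainfall if held) at lags fixed before the analysis.

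Report rate ratios with 95% confidence intervals. State whether the scatterplots show cases or incidence, and at what lag.

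**Route 2: narrow the aim.** Restate it as a description of seasonal and temporal patterns in malaria and climate, without the word *impact*.

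**Cost.** Route 2 is a change of wording. Route 1 needs some extra analysis but no new participants or visits, and the timeline puts final-outcome analysis between March 2025 and December 2026. The population figures it needs should largely be at hand, since mean incidence already requires a denominator. Whether the agency holds rainfall data is not stated. Some subdistricts may have to share a weather series, which reduces the independent climate information and must be reported.

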### Independent Variables of the Study

This study considers demographic and environmental factors as independent variables. Demographic variables include gender, age, education level, occupation, and socioeconomic status (SES). Respondents’ SES will be measured based on ownership of durable assets such as a television, refrigerator, car, electricity, telephone, and radio; the number of bedrooms; and home infrastructure conditions such as access to drinking water sources and the presence of water channels around the house [68]. Using principal component analysis, respondents’ SES will be categorized into 5 quantiles ranging from the lowest (quantile 1) to the highest (quantile 5) [69]. Environmental variables in the study include the location of the residence, categorized as rice fields, coastal areas, or hilly areas, and accessibility to villages, classified as easy, moderate, or difficult to access. Additionally, the study considered proximity to health facilities, including the type and distance of the nearest health facilities. For secondary data from the health center, patient records from 2013 to 2023 were reviewed for all patients with suspected malaria, and positive or negative cases were confirmed based on laboratory examination results. The number of malaria cases based on gender, age group, type of *Plasmodium*, time (year and month), location of residence, and type of treatment and the number of deaths since the period under review were collected from the 4 selected health centers.

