The tenth outcome variable in this study investigates malaria prevalence and malaria-related mortality rates in East Sumba district over the past 10 years (2013-2023). Data on the number of malaria cases and malaria-related deaths were obtained from malaria register books at the health centers and malaria reports from the Health Department of East Sumba District. Therefore, the trends in malaria prevalence and mortality rates over the 10-year period in the study area will be revealed, following the methods of previous studies [79,80].

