For the ninth outcome variable, malaria cases records from 2013 to 2023 will be analyzed across different geographic areas. Data from Baing and Nggongi Public Health Centers, representing coastal regions, will be combined, while records from Mahu and Kananggar Public Health Centers, representing hilly areas, will be aggregated separately. Malaria prevalence will be calculated on a monthly, yearly, and cumulative basis over the study period. To visualize the demographic trends, malaria prevalence will be plotted against key demographic variables. The disparity of malaria prevalence in demographic variables will be investigated using a chi-square test [10,82].

For the tenth outcome variable, descriptive statistics will be used to calculate frequencies and percentages of overall malaria prevalence and trends in malaria transmission considering variations by season, month, year, sex, age, and species of malaria parasite. Epidemiological characteristics, including age group, sex, and *Plasmodium* species–adjusted malaria-related mortality rates in East Sumba District will be presented as percentages followed by their 95% confidence intervals. Chi-square tests will be used to compare the associations of malaria burden by age groups and sex. The malaria prevalence and mortality rate will be illustrated in a map to assess the distributions of the cases geographically [79,80].

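### Outcome 9, and to a lesser degree outcome 10, claim community malaria prevalence from passively recorded cases, which support only test positivity or reported incidence

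*Protocol article*

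**What the plan says.** All references are to the Protocol article.

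**Source.** Under Independent Variables of the Study, the health-center records were "reviewed for all patients with suspected malaria, and positive or negative cases were confirmed based on laboratory examination results".

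**Target, outcome 9.** Outcome Variables describes it as "demographic variations in malaria prevalence among communities residing in hilly and coastal areas", and gives the route: "By analyzing malaria case records from these health centers, this study aims to assess regional disparities in malaria burden". The results are meant to help adapt control efforts to each type of terrain.

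**Statistic, outcome 9.** Statistical Analysis states: "Malaria prevalence will be calculated on a monthly, yearly, and cumulative basis over the study period". It then adds: "The disparity of malaria prevalence in demographic variables will be investigated using a chi-square test".

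**Outcome 10.** Outcome Variables sets out district prevalence and mortality for 2013 to 2023, taken from health-center register books and from Health Department reports. Statistical Analysis presents prevalence as frequencies and percentages and compares burden by age group and sex with chi-square tests.

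**Outcome 8.** For the same kind of case counts, Statistical Analysis says that "the total number of malaria cases and the average malaria incidence will be computed".

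No denominator is named for outcome 9 or 10, and no community parasite survey is described for those years. The limitations, under Principal Findings, do not mention who attends or who is tested.

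**The concern.** Prevalence in a community is the share of its members who are infected at a given time. Estimating it requires observing community members whether or not they seek care. The registers hold only people who came to a health center with suspected malaria. From them one can form positives over tested patients, which is test positivity. With outside population figures one can form cases over resident person-time, which is reported incidence. No choice of denominator turns these records into community prevalence. A cumulative prevalence over several years is less clear still, because the article does not say how repeat records of one person are counted.

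The article itself gives reason to expect selective capture. The Introduction calls appropriate treatment-seeking in the province very low, and Independent Variables of the Study treats village accessibility and distance to a health facility as factors that vary between residents. A contrast between coastal and hilly areas, or between age or sex groups, may therefore reflect attendance and testing rather than infection. It would then be read as a difference in burden and used to direct control.

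**Working it through.** The article states no prevalence or positivity figure, so there is none to reproduce.

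**1. What the article's figures allow.** The Introduction gives 5537 district cases in 2022. Study Population gives 248,776 residents, without a year. Cases over population: 5537 / 248,776 = 0.0223, or 22.3 reported cases per 1000 per year. This is a reported incidence. Positivity cannot be computed because no number tested is given. A point prevalence would need an assumed duration of infection D: 0.0223 × D / 365 gives about 0.04% for D = 7 days and 0.55% for D = 90 days, and still leaves out untested and asymptomatic infections.

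**2. Simple illustration (testing fractions assumed).** Hold the reported rate at 22.3 per 1000 in two areas. If one tests 100 per 1000 residents in a year and the other 200 per 1000, positivity is 22.3 / 100 = 22.3% against 22.3 / 200 = 11.1%. Reported incidence is equal here by construction, so this example shows only the weakness of positivity.

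**3. Fuller illustration (all inputs assumed).** Two groups of N = 10,000 residents each have M = 300 malaria fevers (true incidence 30 per 1000) and F = 3000 other fevers a year. Let s be the fraction of malaria fevers tested and t the fraction of other fevers tested.

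- Positivity = M·s / (M·s + F·t)
- Reported incidence = M·s / N

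| Scenario | s, first vs second group | t, first vs second group | Positivity | Reported incidence per 1000 |
|---|---|---|---|---|
| (a) | 80% vs 40% | 30% vs 30% | 240/1140 = 21.1% vs 120/1020 = 11.8% | 24 vs 12 |
| (b) | 80% vs 80% | 30% vs 60% | 240/1140 = 21.1% vs 240/2040 = 11.8% | 24 vs 24 |
| (c) | 80% vs 40% | 30% vs 10% | 240/1140 = 21.1% vs 120/420 = 28.6% | 24 vs 12 |

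Uncorrected Pearson chi-square on positives and negatives is 33.4 (p = 7e-9) in (a) and 49.2 (p = 2e-12) in (b).

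True incidence is the same everywhere. In (a) both measures show a false difference, and the ratio is larger for reported incidence (24/12 = 2.0) than for positivity (21.1/11.8 = 1.8). In (b) only positivity differs. In (c) the two measures point in opposite directions.

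**The case against.** The strongest reply is that a journal article condenses a fuller protocol, and denominators may be given there or in the method papers cited for these outcomes. That is a fair answer to a complaint about missing detail. It does not answer this point: the article states the target as prevalence in communities and the source as facility records, and any denominator supplied later would still give positivity or incidence. The use of incidence for outcome 8 shows that the labels conflict within the same section.

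Other parts of the reply stand and limit the point. Readers might infer the following, and the document does not support them:

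- **That the chi-square is run on tested patients only.** This is a natural reading of records classed positive or negative, but the base is not stated.
- **That a coastal-hilly test is planned.** The chi-square for outcome 9 is across demographic variables. Coastal and hilly records are aggregated separately and no test between them is named. Outcome 10 has no such contrast, and its source is wider than the health centers, although Health Department reports are still reported cases.
- **That better access makes an area look less affected.** Scenario (b) goes that way if wider testing of other fevers is taken as better access. Scenario (a) goes the other way.
- **That reported incidence cures the problem.** Scenario (a) shows that it does not.
- **That the cumulative figure would be about 24%.** This takes 22.3 per 1000 over 11 calendar years (0.0223 × 11 = 24.5%). It applies one year's rate to the whole period and assumes that yearly values are summed, whereas cumulative may mean pooled.

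**Conclusion.** The point holds as a wrongly named measure. It is firmest for outcome 9, where the community target, the facility source and the chi-square on prevalence are all explicit. It is weaker for outcome 10, which draws on wider reporting.

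The size and direction of any distortion in the real data are unknown, since the article gives no testing or attendance rates. The 10% against 20% example and scenarios (a) to (c) show that care-seeking and testing alone can create or reverse a disparity; they do not estimate one. The 22.3 per 1000 rate joins 2022 cases to a population of unstated year.

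Outcomes 9 and 10 are secondary and use records from 2013 to 2023, before the campaign. The evaluation of the intervention is unaffected.

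**What to change.** 1. Replace prevalence in outcomes 9 and 10 by two named measures: test positivity (positives over suspected patients tested) and reported incidence (confirmed cases per 1000 person-years, using yearly subdistrict population, by age and sex where available).
2. Drop cumulative prevalence, or redefine it as reported incidence pooled over the period. State the period: 2013 to 2023 inclusive is 11 calendar years, while the text speaks of 10.
3. State the base of each chi-square test.
4. Report numbers tested by area and demographic group.
5. Interpret a disparity in burden only with both measures side by side, and state selective attendance and testing as a limitation.

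The cost is rewording, official population counts, and a tabulation of records already reviewed. No new field data are needed. The downside is that the conclusion narrows from community burden to reported burden.
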